#### Preparation:

- One day before surgery a contrast-enhanced CT-scan of the pelvis and abdomen is performed. During the scan three removable electromagnetic marker-patches are placed on the skin at superficial bony structures of the pelvis, such as the anterior superior iliac spine. Locations will be marked precisely with a permanent marker.
- Segmentations and three-dimensional reconstructions are made of the pelvic bone, the iliac vessels, ureters, the tumour, and pathologic lymph nodes using the CT-scan.
- The resulting 3D reconstructions are evaluated by the surgeon who will perform the surgical procedure.

#### In the OR:

- In the OR the patient will be placed on the table according to standard protocol, with the exception that the EM field generator will be placed between the table and the patient (Fig. 1).
- The marker-patches will be positioned at the scan locations and the navigation system will be calibrated.
- The 3D reconstructions will be loaded into the navigation software.
- An intra-operative XPerCT (no contrast fluid used) is acquired to assess the actual patch positions with respect to the 3D model. The XPerCT is used to improve the navigation accuracy.
- Before surgeons start applying the sterile field, an estimate of the registration accuracy between the CT and actual marker positions will be performed. If tolerance limits are exceeded, the navigation procedure during surgery will be cancelled.
- At the moment the laparotomy is advanced to the stage in which the iliac vessels are visible for the surgeon the study measurements are started.
- After the measurements the surgeon will proceed with the standard surgery. If the tumour is rigid, or pathologic lymph nodes are present around the large vessels, the navigation system can be used to localize them.

#### Actual measurements:

- First the surgeon will point the blunt tip probe at the bifurcation of the aorta into the left and right common iliac artery, and also both bifurcations into the internal and external iliac artery. These measurements will be performed without direct

visualization of the navigation system to the surgeon. For each pointed position the estimated position on the navigation system will be stored.

- In the second part, the surgeon will use the navigation system and the probe to localize the ureters. These are generally not visible for the surgeon. The resulting location of ureter tracts will be visually assessed by the surgeon in terms of trueness.

Total time of the proposed preparation and measurements during the surgical procedure will take no longer than 20 minutes. Extra time needed to use the navigation system during surgery will be recorded.

Specific participation for the patient in the study ends during the operation after the measurements have been performed.

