## **6. METHODS**

### **6.1 Main study parameters/endpoints**

During the surgical procedure, iliac vessels and ureters will be identified using the probe. To have an objective measure of accuracy, three locations on the iliac vessel tract will be pointed out by the surgeon without visualization of the navigation system. These points will be the bifurcation of the common iliac artery into the left and right artery, and also both bifurcations into the internal and external iliac artery. The estimated distance of the probe with respect to the bifurcations in the navigation system will be used as accuracy measure. During surgery, the surgeon will search for the ureters and expose them if needed for the surgical procedure. Navigation software and the probe will be used to estimate the tracts of the ureters within the patient. For several tracked positions the actual probe position will be stored in combination with an actual picture of the real situation. The visual measurements in this phase will also be used for assessment of the software usability. Rigid tumours and pathologic lymph nodes along the large vessels will be localized to gain insight in the use of the current navigation system with only external tracking markers. This experience will be used to design a proper clinical study. The addition of an intra-operative XPerCT scan is

---

expected to improve the navigation accuracy. To assess the improvement, we will register the external patches using both the position from the pre-operative CT scan, as well as the position from the XPerCT scan.

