## **8. STATISTICAL ANALYSIS**

### **8.1 Descriptive statistics**

In this registration study, distances will be measured between the estimated probe positions with respect to the bifurcation of the common iliac artery into the left and right artery, both bifurcations into the internal and external iliac artery and ureters. Measurements will be compared within patients to assess patient specific systematic errors, and between patients to assess system specific systematic errors. Due to the nature of a registration study, significance can not be estimated. However, usability and subjective assessment of experience by the surgeons will be valuable for future projects. Assessment of the ureter tracts will be based on the surgeon's opinion, and scored in terms of excellent, reasonable, dubious or wrong. Actual assessment of tumour boundaries and suspected lymph node locations will be recorded and cross-referenced with pathology

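### Ureter distances taken with the navigation screen in use cannot show registration error, and the ureter trueness score is not tied to a ureter that has been seen

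*Protocol*

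**What the plan says.** The protocol describes two measurement procedures.

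- **Iliac vessels.** Section 6.1 says that "three locations on the iliac vessel tract will be pointed out by the surgeon without visualization of the navigation system". It ties the measure it calls objective to these points and defines it as the probe's distance to the bifurcations within the navigation system.
- **Ureters.** In the second part of the measurements (Section 5.1, Actual measurements), "the surgeon will use the navigation system and the probe to localize the ureters. These are generally not visible for the surgeon". The outcome there is a judgement: "The resulting location of ureter tracts will be visually assessed by the surgeon in terms of trueness". Section 6.1 adds that "the surgeon will search for the ureters and expose them if needed for the surgical procedure", and that for several tracked positions the probe position is stored together with a picture.

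Section 8.1 brings the two together. Its distances run to the aortic bifurcation and to "both bifurcations into the internal and external iliac artery and ureters". Their use is stated: "Measurements will be compared within patients to assess patient specific systematic errors, and between patients to assess system specific systematic errors". The ureter tracts are also "scored in terms of excellent, reasonable, dubious or wrong", on the surgeon's opinion.

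Section 5.2, on inaccuracies of the system, says that only regions that can be seen and approached will be localized. The main endpoint in Section 6.1 names identification of both the iliac vessels and the ureters.

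**The concern.** A distance between probe and structure measures system error only if the probe was placed independently of the system. That holds for the bifurcations, where the surgeon touches a visible landmark without seeing the screen. It does not hold for the ureters as written. The surgeon steers the displayed probe towards the displayed, CT-segmented ureter, so a distance then read from the same display describes how well the surgeon followed the screen.

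The score has a related gap. The surgeon who has just navigated gives it, the ureter is generally hidden at that moment, and it is exposed only if the operation requires it. No step delays the score until the ureter has been seen, and the scale has no level for a ureter that never was.

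At stake is what the study can say about the ureter, one of two structures named in the main endpoint. Section 5.2 lists misguidance through unforeseen inaccuracy among the major risks. The Summary makes proof that the system is safe and accurate the condition for further studies.

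**Working it through.** The protocol states no figure for ureter accuracy, so there is nothing to reproduce. The check sets out what each procedure can measure.

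**Inputs**

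- Guided placement for ureters, screen-hidden placement for bifurcations: Sections 5.1 and 6.1.
- In-system distance: Section 6.1, defined there for the bifurcations only. Applying it to the ureters is an assumption.
- *R*, the 3D root-mean-square registration error at the ureter: not given, varied from 0 to 20 mm. The registration limit in Section 5.2 (1.0 cm) serves only as a scale, because it applies at the skin sensors.
- *h*, the 3D root-mean-square pointing noise: not given, assumed 1 or 3 mm.

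**Model.** Let *e* be the registration error and *p* the pointing error, independent and normal, with standard deviation R/√3 and h/√3 per axis. The ureter is locally a line, so only the two perpendicular components count.

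- Guided, displayed distance: |p|. The error *e* does not enter.
- Guided, true distance to the real ureter: |p − e|.
- Screen hidden, probe on an exposed ureter, displayed distance: |p + e|.

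The mean length of a two-component normal vector with per-axis standard deviation *s* is s√(π/2) = 1.2533 s. Hence:

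- mean guided displayed distance = 1.2533 × h/√3, which is 0.7 mm for h = 1 and 2.2 mm for h = 3;
- mean guided true distance = mean screen-hidden distance = 1.2533 × √((R² + h²)/3).

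| R (mm) | Guided, displayed (h = 1 / h = 3) | Guided true, or screen-hidden displayed (h = 1 / h = 3) |
|---|---|---|
| 0 | 0.7 / 2.2 | 0.7 / 2.2 |
| 2 | 0.7 / 2.2 | 1.6 / 2.6 |
| 5 | 0.7 / 2.2 | 3.7 / 4.2 |
| 10 | 0.7 / 2.2 | 7.3 / 7.6 |
| 20 | 0.7 / 2.2 | 14.5 / 14.6 |

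For example, at R = 10 and h = 1: 1.2533 × √(101/3) = 1.2533 × 5.80 = 7.3 mm. A simulation with 200,000 draws agrees to within 0.1 mm. In it the correlation of the guided displayed distance with the registration error is about 0.00.

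If tissue keeps the probe off the ureter, the displayed gap is not near zero. It then contains an unknown tissue depth, and any registration error in that direction cannot be separated from it.

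**Reference for the score.** The exposed fraction is not stated. If 10%, 25%, 50% or 75% of the maximum of 95 patients had an exposed ureter, the reference would exist in 9.5, 23.75, 47.5 or 71.25 patients, that is, about 10, 24, 48 or 71.

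**The case against.** The strongest reply is that the protocol already separates objective from subjective measures. The objective label is kept for the screen-hidden iliac points, the ureter score is openly the surgeon's opinion, and the ureter phase also serves to assess usability. The study is a proof of principle that disclaims significance, accuracy is a secondary objective, and no decision rule uses the ureter results. Section 8.1 does not say how the ureter distance is obtained. Section 6.1 has the surgeon search for the ureters and stores pictures, and Section 5.2 limits localization to visible regions. A *not verified* category and denominators could sit in an analysis plan or case report form.

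Much of this stands, and it limits what may be claimed. Three stronger readings are tempting.

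- *The ureter distance is zero by construction.* This follows only if the in-system distance is taken at guided points with the probe on the displayed ureter. A distance to an exposed ureter would be different, but no such step is written.
- *Accuracy will look about a third better than it is.* Averaging three bifurcations with true error m and two guided ureter points with a 1 mm residual gives (3m + 2)/5: 3.4 mm at m = 5 and 6.4 mm at m = 10, or 32% and 36% lower. No section plans such a mean, and two points and 1 mm are assumptions. With a 3 mm residual the reductions are 16% and 28%; with 5 mm, 0% and 20%.
- *Most ureters are scored unseen.* The text makes this plausible, but the exposure rate is not given.

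What does not stand is that an analysis plan could repair the matter. If no screen-hidden point is taken and nobody records whether the ureter was seen, later analysis cannot supply either. The pictures help only where the ureter is visible, and no rule links them to the score. The visibility statement in Section 5.2 conflicts with Section 5.1, so it cannot settle the point.

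**Conclusion.** The point holds in a conditional and limited form. Section 8.1 uses ureter distances to assess systematic error, while the only written ureter procedure is screen-guided. If the distance is the in-system one of Section 6.1, it gives no usable information on registration error: under the stated model its mean is the same at every error from 0 to 20 mm. The millimetre values rest on the assumed *h* and *R*. The absence of any dependence on registration error does not, provided the probe can be brought to the displayed ureter; otherwise tissue depth obscures the error.

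The trueness score is unblinded and not tied to a ureter that has been seen, in a proportion of patients that the protocol does not allow one to estimate. The screen-hidden iliac measure is unaffected, and no percentage bias in overall accuracy can be given. The correction matters because it changes what can be concluded about a structure named in the main endpoint.

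**What to change.** 1. In Section 8.1, remove screen-guided ureter points from the distance and systematic-error analysis.
2. In Sections 5.1, 6.1 and 8.1, give the trueness score only after the ureter has been seen. Otherwise record *not verified*, and report both counts.
3. Where the ureter is already exposed for the operation and the 20-minute limit allows, record one screen-hidden probe point per side. Report the perpendicular distance to the CT-segmented ureter, and state that it cannot detect error along the tract.
4. Reconcile Section 5.1 (ureters generally not visible) with Section 5.2 (only visible regions localized).

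The cost is one case report form category, at most two extra probe touches in some patients, and revised wording. Step 3 depends on timing: Section 5.1 places the measurements before standard surgery proceeds and ends participation once they are done. A ureter exposed later would therefore fall outside the present sequence. A delayed score under step 2 meets the same limit, so the sentence on the end of participation needs matching wording. The downside is fewer scored ureters and possibly less favourable results.

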### Primary Objective:

Feasibility and safety of an in-house developed electromagnetic navigation system during abdominal surgery.

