## **5.2 Investigational products**

The navigation system used for this study is composed of elements of the Aurora Electromagnetic Measurement System from Northern Digital Inc. (Waterloo, Ontario, Canada) and is combined with in-house developed software for the navigation and visualisation. The system is developed for use in the NKI-AvL only, and there is no current intent to commercialize the system. According to Dutch national guidelines (beleidsplan medische apparatuur), and agreements between the METC and the department of clinical physics, a tailored safety management and risk assessment protocol should be followed which is adapted to the specific medical device.

For technical validation of the navigation system before start of the study we will provide:

- A risk assessment, in collaboration with [name] (Clinical physicist)
- A detailed description of the medical device and software, together with a report of pre-clinical tests on system accuracy, in collaboration with [name] (Clinical physicist)
- A report on electrical safety, in collaboration with [name] (Electrical safety officer)
- A safety protocol for sterile use of the probe and reference markers in collaboration with [name] (Sterile safety officer)
- A detailed operating manual for use in the OR, in collaboration with [name] (Teamleader OR)

After all protocols and manuals have been approved, approval of [name] (head of clinical physics department) will allow the use of the navigation system for the study.

The major risk domains for the current study are electrical safety, sterility, and unforeseen inaccuracies leading to misguidance of the surgeon.

The NDI Aurora hardware has been embedded in several commercial navigation systems, such as the Philips Percunav system. Electrical safety is extensively tested and described by NDI, and will be independently validated by [name].

Two components of the system will come in contact with the patient, being the reference patches and the blunt tip probe. The reference patches are developed by Philips in collaboration with NDI, and are provided in a sterile package. The blunt tip probe can withstand autoclave procedures, and will be tested on sterility by [name]. An alternative option is to use a sterile cover which is also used for hand-held ultrasound probes.

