### **7.3 Follow up of adverse and serious adverse events**

All adverse events will be followed up until they have abated, or until a stable situation has been reached. Depending on the event, follow up may require additional tests or medical procedures as indicated, and/or referral to the general physician or a medical specialist.

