### **8.4 Benefits and risks assessment, group relatedness**

Because of the nature of this study, we do not expect any adverse events to occur that are related to the intervention. Measurements shall only be performed during the scheduled operation under full anesthesia and physical monitoring.

Collected data will not be provided to surgical physicians. Moreover, planned surgical procedure will not be influenced by the measurements and hence patient treatment will not

---

be influenced by the measurements. Subjects who participate in the test will not benefit from the test nor experience unacceptable additional discomfort.

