### **9.4 End of study report**

The sponsor will notify the accredited METC of the end of the study within a period of 8 weeks. The end of the study is defined as the end of the last patient's procedure.

Within one year after the end of the study, the investigator will submit a final study report with the results of the study, including any publications/abstracts of the study, to the accredited METC.

---

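### Safety is a primary objective, but the protocol fixes no adverse-event ascertainment period and its passages on when observation ends conflict, so post-operative harms would be captured only haphazardly

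*Protocol*

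**What the plan says.** Section 2 of the protocol gives the primary objective as "Feasibility and safety of an in-house developed electromagnetic navigation system during abdominal surgery". Section 5.1, under the actual measurements, then says "Specific participation for the patient in the study ends during the operation after the measurements have been performed". Section 9.4 adds "The end of the study is defined as the end of the last patient's procedure".

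Other passages reach further:

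- Section 5.1, on the steps in the operating room, says of the stage after the measurements: "If the tumour is rigid, or pathologic lymph nodes are present around the large vessels, the navigation system can be used to localize them".
- Section 7.2 records all adverse events that the subject reports or the staff observe. It gives no start or end date for collection.
- Section 7.3 says "All adverse events will be followed up until they have abated, or until a stable situation has been reached".
- Section 8.1 compares recorded tumour boundaries and node locations with pathology, which is available only after surgery.

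On risk, section 5.2 says "The major risk domains for the current study are electrical safety, sterility, and unforeseen inaccuracies leading to misguidance of the surgeon" and notes that inaccuracy could lead to disrupted anatomy. The main endpoint in section 6.1 assesses feasibility and safety through identification of the iliac vessels and ureters. It names no safety event and no time window.

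**The concern.** Two of the three named risk domains can produce harm that shows itself only after the operation. A sterility failure would appear as infection. An injury from misguidance may be recognised late, and section 1 describes reintervention and long-term morbidity as consequences of ureteric damage. Under 5.1 and 9.4 as worded, nobody is assigned to look for these harms after the measurements. Under section 7 they should be recorded if they come to notice. Which reading applies is left to whoever fills in the record.

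Two things depend on this. Sections 6.4 and 7.2 end the study if a related serious adverse event occurs. With no data safety monitoring board (7.4) and no planned monitoring visits (6.5), that rule is the main event-based safeguard, and it works only if events are ascertained. The Summary also makes further studies conditional on the system being shown to be safe and accurate, so the safety count will be read as evidence.

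**Working it through.** The plan states no safety rate, margin or sample size calculation, so there is no figure to reproduce. The check sets the passages side by side and then asks how much a low count could show.

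**Where observation ends**

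| Source | What it implies |
|---|---|
| 5.1, actual measurements | Participation is over in theatre, after the measurements |
| 5.1, in the OR | Navigation may still be used after the measurements |
| 7.2 | Adverse events recorded, no cut-off; serious-event criteria include prolonged hospital stay |
| 7.3 | Detected events followed to resolution or stability |
| 8.1 | Post-operative pathology is used |
| 9.4 | Study ends with the last procedure |

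Rows 1 and 6 cannot be applied literally together with rows 2 to 5. Device use may itself continue past the stated end of participation. Section 8.4 places the measurements under full anaesthesia, so spontaneous reporting of harm from them presupposes a post-operative period that no passage defines. Section 7.3 governs events already found; it does not cause them to be found.

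**Which named risks are affected**

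- Electrical safety: events occur in theatre, inside the window.
- Misguidance: injury recognised at once is inside the window; injury recognised later is not systematically covered.
- Sterility: infection appears after surgery and is not systematically covered.

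**What a zero count could show**

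For zero events in n patients the exact upper limit is 1 − α^(1/n).

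- n = 95 (the maximum in 4.4): 1 − 0.05^(1/95) = 3.1% one-sided; 1 − 0.025^(1/95) = 3.8% as the upper end of a two-sided 95% interval.
- n = 67, if the 30% failure allowance in 4.4 applied to everyone (an assumption; the protocol states it for the 20 added patients; 95 × 0.70 = 66.5): 4.4% one-sided, 5.4% two-sided.

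These limits assume that every event is seen. If only a share s of late harms is captured, the limit applies to s times the true rate, so the limit on the true rate is 3.1%/s. The documents give no s. Over an assumed range:

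| s | One-sided 95% limit, n = 95 |
|---|---|
| 1 | 3.1% |
| 0.5 | 6.2% |
| 0.25 | 12.4% |
| 0 | no limit |

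**Background scale only**

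Section 1 gives ureteric damage as 0.5% to 10%. In 95 patients that is 95 × 0.005 = 0.5 to 95 × 0.10 = 9.5 cases. The chance of at least one, 1 − (1 − p)^95, is 38% to above 99.9%. These are rates for the surgery, not for the device. They show that such events may well occur in the cohort and would need to be recorded and assessed for a link to the study.

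**The case against.** The strongest reply is that the sentence in 5.1 sits among the study procedures and is naturally read as saying that the study-specific measurements are finished. It does not say that adverse-event recording stops. Section 7.2 has no cut-off, and several of its serious-event criteria describe post-operative outcomes. For every patient but the last, the study remains open after the operation. This stands, and it makes the defect one of conflict and omission rather than deliberate exclusion.

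A reader might infer that all the harms the protocol names fall outside observation, or that the study is bound to report zero events. The documents support neither. Electrical events and injuries seen at once are inside the window, and nothing shows what share of harms appears later. Nor do the section 1 rates, including the figure of about 30% for hypogastric plexus damage, measure device harm: they are background surgical rates, the study has no comparison group, and the plexus is not a navigation target.

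A second reply is that exposure is low-risk. Section 5.2 says navigation is not used blindly and is limited to visible, approachable regions, with tolerance limits that cancel the procedure. Section 8.4 says "Collected data will not be provided to surgical physicians" and that treatment is unaffected. The limits are real mitigation. But 5.1 has the surgeon use the system to localise ureters that it describes as generally not visible, so these reassurances cannot be taken at face value until the passages agree.

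A third reply is that case report forms or device safety documents may list safety items. They may, but they would not resolve the conflict over when participation and the study end.

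**Conclusion.** The point holds as a conflict between passages and a missing ascertainment period. Safety is primary, yet the protocol does not say how long patients are observed for harm, and its statements on the end of participation and of the study disagree with those on later navigation use, adverse events and pathology. Infection from a sterility failure and late-recognised misguidance injury would be captured unsystematically.

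The size cannot be given as a number of missed events, because the documents give neither device-related rates nor the share of harms that appears late. What can be said is that a zero-event limit of 3.1% one-sided or 3.8% two-sided at n = 95 applies only to ascertained harms and to patients actually exposed. It weakens in proportion to any under-capture and with a smaller denominator. The number navigated may be below 95, given the drop-out and failure allowance in 4.4, the cancellation rules in 5.2 and withdrawal for technical problems in 6.3.

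The conclusion rests on the text as worded and on the premise that these two kinds of harm can surface after the operation.

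**What to change.** 1. Reword 5.1 to say that only the study measurements end in the operating room, and that safety ascertainment continues to one fixed post-operative point chosen by the sponsor. Make the text consistent with navigation use after the measurements, with 7.2 and 7.3, and with the pathology comparison in 8.1.
2. Redefine the end of study in 9.4 as the date on which the last patient reaches that point.
3. Name a short list of safety items, such as ureteric or vascular injury, infection and reintervention. Collect them from routine records for every patient exposed to any study procedure, including those whose navigation was cancelled or who were withdrawn under 6.3.
4. Report safety with that denominator, show the number actually navigated separately, and state that any upper limit covers only the items ascertained.
5. Reconcile 8.4 (data withheld from surgeons, treatment unaffected) and 5.2 (visible regions only) with the ureter step in 5.1.

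The cost is amendment wording, a short chart review and a study end later by the length of the window. If routine records suffice, no extra visits are needed.
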